## Abstract

**Background:**

Communities of practice are based on the idea that learning involves a group of people exchanging experiences and knowledge. The e-MPODERA project aims to assess the effectiveness of a virtual community of practice aimed at improving primary healthcare professional attitudes to the empowerment of patients with chronic diseases.

**Methods:**

This paper describes the protocol for a cluster randomized controlled trial. We will randomly assign 18 primary-care practices per participating region of Spain (Catalonia, Madrid and Canary Islands) to a virtual community of practice or to usual training. The primary-care practice will be the randomization unit and the primary healthcare professional will be the unit of analysis. We will need a sample of 270 primary healthcare professionals (general practitioners and nurses) and 1382 patients. We will perform randomization after professionals and patients are selected. We will ask the intervention group to participate for 12 months in a virtual community of practice based on a web 2.0 platform. We will measure the primary outcome using the Patient-Provider Orientation Scale questionnaire administered at baseline and after 12 months. Secondary outcomes will be the sociodemographic characteristics of health professionals, sociodemographic and clinical characteristics of patients, the Patient Activation Measure questionnaire for patient activation and outcomes regarding use of the virtual community of practice. We will calculate a linear mixed-effects regression to estimate the effect of participating in the virtual community of practice.

**Discussion:**

This cluster randomized controlled trial will show whether a virtual intervention for primary healthcare professionals improves attitudes to the empowerment of patients with chronic diseases.

**Trial registration:**

ClicalTrials.gov, NCT02757781. Registered on 25 April 2016.

**Protocol Version**. PI15.01 22 January 2016.

**Electronic supplementary material:**

The online version of this article (doi:10.1186/s13063-017-2232-9) contains supplementary material, which is available to authorized users.

## Background

Increased life expectancy has contributed to the growing prevalence of chronic diseases. Different European studies report that chronic diseases affect more than 80% of people aged over 65 years, are responsible for 86% of deaths and generate premature morbidity and loss of years of healthy life [1]. The growing burden of these diseases also has massive economic consequences, ranging from the impoverishment of individuals and families to a considerable increase in healthcare system costs and the potential weakening of economies [2]. It has been estimated that 70–80% of healthcare costs in Europe are currently allocated to chronic disease management [3].

These important epidemiological changes are pushing multiple healthcare reforms across Europe, aimed at enhancing sustainability and transforming healthcare systems — from a focus on acute-care needs to a focus on chronic and multiple diseases. A key trend in these reform processes is the inclusion of the key concept of patient empowerment [4].

Although there is no single generally accepted definition of patient empowerment, most definitions focus on the ability of individuals to make decisions about their health (behaviour) and to take control of health-related aspects of their lives [5, 6].

A recently proposed definition in the European context is that used for the EMPATHIE project, led by the Instituto Universitario Avedis Donabedian [7]: An empowered patient has control over the management of their disease on a daily basis, acts to improve their quality of life and has the necessary knowledge, skills, attitudes and perceptions to adjust their behaviour — and work in partnership with others when necessary — to achieve optimal wellness. Interventions aimed at empowerment aim to equip patients (or their informal caregivers, as appropriate) with the ability to participate in decisions about their illness to the degree they wish, to become co-managers of their disease in partnership with healthcare professionals, and to develop self-confidence, self-esteem and the skills necessary to deal with the physical, emotional and social impact of the disease on their daily lives.

There are a number of prerequisites for patient empowerment, but two of the most important are a certain level of health literacy and the support of professionals [8], given that the attitude of professionals is widely acknowledged as a key variable in achieving patient empowerment [9]. More patient-centred healthcare professionals are not only more likely to empower patients managing chronic diseases [10, 11], but also to enhance patient satisfaction and improve adherence to treatments [12–14].

The Eurobarometer Qualitative Study on Patients Involvement [15] found that most healthcare professionals consider themselves to be primarily responsible for the health of their patients. Only when directly asked did they concede that patients also held some responsibility, in that they could adopt healthy lifestyles or preventive measures, provide information to assist diagnoses and comply with the instructions of healthcare professionals. Most professionals felt that patient involvement improves care quality by helping patients feel more motivated to take better care of themselves, better understand their disease and its treatment and better monitor their health independently. Healthcare professionals need to increase their awareness of patients’ capacities to assume a more active role in their own care and to learn mechanisms that increase this capacity.

The community of practice (COP) was described in 1991 by Lave and Wenger [16] as a “group of people who share an interest, a set of problems or a passion about a topic, and who deepen their knowledge and experience in the area through continuous interaction that strengthens relationships.”

In COPs, therefore, which are based on the concept of lifelong learning, learning involves exchanges of experiences and knowledge between people. COPs differ from conventional working groups in several ways [17]: (1) member participation is voluntary and reflects a common interest; (2) COPs are informal, but although there is no hierarchy, they do have a structure; (3) learning is viewed as a process of participation and shared leadership; and (4) COPs are flexible and generally interconnect with other groups within or outside the organization. Several authors have written about the positive impact of COPs in improving the quality of care [17–19]. In the healthcare environment, active social interaction, knowledge sharing, knowledge creation and the construction of identity by COP members are, as in other similar environments, key elements [20, 21].

Although COPs as a means of learning are still relatively novel in health care [16], since 2005 there has been a notable increase in publications on the topic [22–26], although the scientific evaluation of their results is not systematic. A common problem is the lack of baseline and comprehensive longitudinal tracking. To our knowledge, no clinical trial testing the effectiveness of virtual communities for healthcare professionals has been published to date.

This project proposes an approach with a triple benefit: increasing knowledge of empowerment among professionals, harnessing the potential benefit of COPs as an innovative educational tool and rigorous assessment of the instrument e-MPODERA.

This protocol has been prepared in accordance with the Standard Protocol Items: Recommendations for Interventional Trials (SPIRIT) checklist and figure (Additional file 1 and Fig. 1).

**Fig. 1 Fig1:**
[figure not shown]
Standard Protocol Items: Recommendations for Interventional Trials (SPIRIT) study timeline

## Aim

This article describes the design of a project called Effectiveness of a Virtual Intervention to Improve Healthcare Professional Attitudes to Patient Empowerment (e-MPODERA). Our main aim was to evaluate the effectiveness of a COP in improving attitudes of primary healthcare professionals to the empowerment of patients with chronic diseases, as measured using the Patient Practitioner Orientation Scale (PPOS) questionnaire [27]. As a secondary aim we also evaluated the effectiveness of a COP in improving the activation of patients with chronic diseases, as measured using the Patient Activation Measure (PAM) questionnaire [28]. We hypothesize that a virtual COP intervention will improve primary healthcare professional attitudes to empowering patients with chronic diseases.

## Methods

### Design

This is a multicentre pragmatic clinical trial, with two parallel arms comparing the intervention with usual training, with randomized allocation by clusters.

### Setting

The setting is in primary-care practices (PCPs) — clusters — from three regions of Spain (Catalonia, Madrid and the Canary Islands).

### Participants

#### PCPs (clusters)

Urban or rural PCPs located in Catalonia, Madrid or the Canary Islands, willing to participate and with adequate Internet connectivity that enables access to the COP.

#### Primary healthcare professionals

The primary healthcare professionals involved in the study will be general practitioners (GPs) and nurses working in the selected PCPs who volunteer to participate in the study after signing informed consent. Healthcare professionals who participate in the study should have no intention of moving from their practice during the study period.

#### Patients

Inclusion criteria are: (1) patients aged 18 years and older; (2) patients whose electronic medical records include an active diagnosis, made at least one year prior to inclusion in the study, of any of the following chronic diseases: hypertension, diabetes mellitus, hypercholesterolaemia, obesity, heart failure, ischaemic heart disease, cerebrovascular disease, chronic renal disease, chronic obstructive pulmonary disease or asthma; (3) patients who have consulted their GP or nurse about their chronic disease at least twice in the previous 12 months; and (4) patients who have signed the informed consent for participation in the study. Exclusion criteria are: (1) patients unlikely to cooperate with the study; (2) patients with a temporary residency; (3) patients who are institutionalized; (4) patients with terminal illnesses; (5) patients with a physical or mental disability that prevents them from responding suitably to questionnaires; and (6) patients whose telephone or email details for later contact are not in the PCP dataset.

### Sample size

We calculated the required number of primary healthcare professionals for the purpose of comparing two independent means, considering as significant a post-intervention mean difference of 0.2 points and a common standard deviation of 0.5 points in the PPOS questionnaire between the e-MPODERA virtual COP intervention and control groups [29]. Each group will need 100 professionals, assuming alpha error of 0.05 and power of 80%. Since we will randomize by clusters, we have adjusted the sample size to take into account the design effect. Considering an intraclass correlation coefficient of 0.03 and assuming an average size per cluster of five healthcare professionals, we obtained a design effect of 1.12 [30]. Given these assumptions and expecting 20% loss to follow up after 12 months, we calculated a sample size of 270 healthcare professionals (135 professionals per group). The recruited healthcare professionals will, in turn, recruit a total of 1382 patients (assuming 20% loss to follow-up), the number that is required to detect a mean difference between the two groups of 4 points in the Patient Activation Measure questionnaire (PAM) scale [28].

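### On the protocol's own inputs, 20% loss requires 280 professionals; the stated 270 covers 17% loss, a minor shortfall

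*Protocol article*

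**What the plan says.** The Sample size section of the protocol article sizes the trial on the primary outcome, the PPOS score, as a comparison of two independent means. The target is given as "considering as significant a post-intervention mean difference of 0.2 points", with "a common standard deviation of 0.5 points in the PPOS questionnaire". Before any inflation, "Each group will need 100 professionals", at an alpha of 0.05 and 80% power.

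The section then adjusts for clustering: "Considering an intraclass correlation coefficient of 0.03 and assuming an average size per cluster of five healthcare professionals", which it reports as a design effect of 1.12. The last step adds the allowance for attrition: "expecting 20% loss to follow up after 12 months, we calculated a sample size of 270 healthcare professionals (135 professionals per group".

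The Methods paragraph of the Abstract repeats the total: "We will need a sample of 270 primary healthcare professionals (general practitioners and nurses) and 1382 patients". The article gives no other loss rate for professionals and does not show how the 20% was applied.

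**The concern.** An allowance for loss has to leave the required number of evaluable participants after the loss has occurred. If a fraction d is lost, the recruited number must be the requirement divided by (1 − d). Multiplying by (1 + d) always gives too few, because the loss acts on the larger, recruited number and not on the requirement.

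The final figure of 135 per group looks like the result of multiplication. If so, the recruitment target does not deliver what the sentence claims for it, namely the planned power after 20% loss at the stated design effect. At stake is the accuracy of the power statement for the primary outcome, and how much attrition the trial can bear before it falls below its own requirement.

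**Working it through.** **Inputs.** All are from the Sample size section, except the number of practices (54), which is under PCP recruitment and Randomization.

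- Difference δ = 0.2; standard deviation σ = 0.5
- Alpha 0.05, power 80%. Sidedness is not stated. Two-sided is inferred, because a one-sided test would need only 78 per group.
- Stated n before inflation: 100 per group
- Intraclass correlation 0.03; mean cluster size 5
- Loss to follow-up 20%
- Stated result: 135 per group, 270 in all

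**Step 1: n per group before inflation.** n = 2(1.96 + 0.8416)² × 0.5²/0.2² = 98.1, or 99 after rounding up. The t-based calculation gives 100, which matches the protocol.

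**Step 2: design effect.** 1 + (5 − 1) × 0.03 = 1.12, as stated. The evaluable requirement is 100 × 1.12 = 112 per group, 224 in all.

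**Step 3: reproducing the stated total.** 112 × 1.2 = 134.4, rounded up to 135 per group, or 270 in all. This matches exactly.

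**Step 4: the allowance that 20% loss requires.** 112/(1 − 0.20) = 140 per group, or 280 in all. The stated total is 10 lower; 10/270 = 3.7%.

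**Step 5: what 270 covers.** The largest loss that still leaves 112 of 135 is 1 − 112/135 = 17.0%. At 20% loss, 135 × 0.8 = 108 per group remain, 4 short of 112.

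**Step 6: power at 20% loss.** By the normal approximation, power = Φ(δ/(σ√(2/n)) − 1.96), where n is the effective number per group (evaluable number divided by design effect).

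| Recruited per group | Retained | Design effect | Effective n | Power |
|---|---|---|---|---|
| 140 | 112 | 1.12 | 100.0 | 80.7% |
| 135 | 108 | 1.12 | 96.4 | 79.3% |
| 135 | 108 | 1.09 | 99.1 | 80.4% |

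The last row recomputes the design effect for four professionals retained per practice: 1 + (4 − 1) × 0.03 = 1.09. On an ordinary t basis the three powers are 80.4%, 78.9% and 80.0%. On either basis the cost of the shortfall at 1.12 is about 1.4 to 1.5 percentage points.

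**The case against.** The strongest reply is that the design effect should itself be updated for the loss. If 20% are lost evenly, a practice of five becomes a practice of four and the design effect falls to 1.09. Starting from 99 per group, 99 × 1.09/0.8 = 134.9, which rounds up to exactly 135. On that reading 270 keeps about 80% power. This stands as a limit on the practical consequence. It does not rescue the text, which states 100 per group and 1.12. With 100 and 1.09 the requirement is still 100 × 1.09/0.8 = 136.25, above 135. With 1.12 retained, starting from the unrounded 98.1 or from 99 gives 276 or 278 in all, also above 270.

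A second reply is that 270 is simply 54 practices × 5 professionals. That is possible, and it is why a reader who infers that multiplication by 1.2 is an established fact goes further than the document allows. But the Sample size section presents 270 as calculated from its assumptions and the expected loss. Whatever its origin, the number does not follow from them.

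A third reply is that the analysis imputes missing data by last observation carried forward, so nobody is lost. The section on data collection, management and analyses also promises results without imputation, where the loss applies in full. PPOS is measured only at baseline and 12 months, so carrying the baseline forward gives a lost professional a change of zero, which would dilute any difference.

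A reader might also infer that the 1382 patients were inflated in the same way. The protocol gives no standard deviation, intraclass correlation or pre-loss number for the patient calculation, so this cannot be tested and is not claimed.

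**Conclusion.** The point holds as a minor arithmetic error. On the stated inputs (100 per group, design effect 1.12, 20% loss) the requirement is 140 per group and 280 in all, against 135 and 270. The loss actually covered is 17.0%.

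At 20% loss and a design effect of 1.12, power is about 79% against 80.7% for the correctly inflated number on the same normal approximation. If the design effect falls to 1.09 because four per practice are retained, power is about 80%. These figures assume a two-sided test, equal groups, evenly spread loss and the protocol's own values for the difference, standard deviation and intraclass correlation.

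A reader might infer that the trial is materially underpowered. The document does not support that: the gap is 10 professionals and between one and two points of power, and it largely disappears once the design effect is updated. Lower power figures could be produced by basing the degrees of freedom on the number of practices, but that is a separate refinement. It would lower the correctly inflated design as well, so it must not be set against 80.7%.

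**What to change.** Keep 270 and correct the sentence in the Sample size section. Wording along these lines would do: 270 professionals (135 per group) allow for a loss of 17% at a design effect of 1.12; if 20% are lost, 108 per group remain and power is about 79% (about 80% if the design effect falls to 1.09 with four professionals retained per practice). The Abstract can keep 270 unchanged.

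The cost is one sentence and a slightly less favourable power statement. No extra enrolment is asked for. Reaching 280 would take 280/5 = 56 practices, or 280/54 ≈ 5.2 professionals in each of the 54 planned, which the size of the shortfall does not warrant when recruitment is already under way.

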### Recruitment

Table 1 depicts the various stages of the e-MPODERA trial.

**Table 1 Tab1:** e-MPODERA randomized controlled trial stages

Stage	Procedure	
Stage 1 1^st^ month	Face-to-face or virtual meetings with the selected PCPs in each of the 3 Spanish regions. Invitation to participate. Participation agreement form signed by the PCP director	
Stage 2 1^st^ month	Face-to-face or virtual meetings in each selected PCP. Invitation to participate. Informed consent form signed by professionals who agree to participate	
Stage 3 2^nd^ month	PAM questionnaire administration to all eligible patients (baseline)	
Stage 4 2^nd^ month	PPOS questionnaire administration to all included professionals (baseline)	
Stage 5 2^nd^ month	PCP randomization	
Stage E 6 2-13^th^ month	Intervention group Virtual community of practice	Control group Usual training
Stage 7 14^th^ month	PPOS questionnaire administration to all included professionals (post intervention)	
Stage 8 14 − 15^th^ month	PAM questionnaire administration to all eligible patients (post intervention)	

*PCP* Primary-care practice, *PAM* Patient Activation Measure, *PPOS* Patient-Practitioner Orientation Scale

#### PCP recruitment

From the total pool of PCPs in Catalonia (329), Madrid (262) and the Canary Islands (102), we will randomly select 18 PCPs from each participating region (total 54 PCPs) using computer-generated random tables. We will contact the selected PCPs by e-mail/telephone to briefly explain the study and to request their participation and will subsequently provide a more detailed explanation of the study in face-to-face or virtual meetings of PCP directors or designated professionals. We will randomly assign PCPs that agree to participate to either the e-MPODERA virtual COP intervention group or the control (usual training) group. Before randomization we will request PCP directors to sign a participation agreement.

#### Professional and patient recruitment

We will hold face-to-face or virtual meetings with GPs and nurses from each selected PCP. Before PCP randomization, all included professionals (at least one per cluster) will complete both an informed consent form (Additional file 2) and the PPOS questionnaire, so as to minimize possible information bias. Also before PCP randomization, to avoid possible selection bias, the participating healthcare professionals will consecutively include patients. Patients who meet the inclusion criteria will complete, in their first visit, both an informed consent form (Additional file 3) and the PAM questionnaire.

### Randomization

We will perform allocation by clusters — with the PCP as the randomization unit — to minimize possible contamination effects among professionals. An investigator blinded to PCP identity and to baseline PPOS and PAM results will centrally perform randomization after professionals and patients are selected. This investigator will randomly assign 54 PCPs (nine pairs for each of the three regions, each randomly assigned a code) to either the e-MPODERA virtual COP group or the control group (27 PCPs per group) using Epidat 4.1 software (balanced group option). The unit of analysis will be the primary healthcare professional. To reach the necessary sample size, each professional will be required to recruit at least six consecutive patients. Figure 2 depicts a flowchart of the randomization procedure.

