### Data collection, management and analyses

We will collect a mixture of professional and patient-reported data, using validated questionnaires for the primary and most of the secondary outcome measures. We will require each recruiting site to keep accurate and verifiable source notes regarding each participant’s inclusion and continued participation in the study. We will collect, transfer and store data in accordance with Good Clinical Practice (GCP) guidelines and data protection requirements. The e-MPODERA standard operating procedures (SOPs) and study data management plan will define the exact procedures for collecting, transferring, storing and quality-controlling study data.

We will perform descriptive and exploratory analyses, including cluster analyses according to participant baseline characteristics, using means and standard deviations for continuous variables and proportions for categorical variables. We will compare the two groups in terms of PPOS scores, PAM scores and descriptive variables. We will perform inferential analysis using the Mann-Whitney U test — with a 95% confidence interval — to compare across-group results in the PPOS and PAM tests in terms of score at 12 months from baseline.

We will perform a multilevel analysis of models for the main outcome (the PPOS test), where the response variable will be the difference between initial and final scores in the questionnaire administered to participating professionals and the explanatory variable will be the dichotomous intervention variable (1 = COP/0 = control). This model considers covariates such as age, sex and professional profile and also takes into account the random effect associated with the COP. We will use the propensity score to control for possible selection bias and enhance the accuracy of the model.

We will perform intention-to-treat analyses using the statistical software (http://www.R-project.org/) and PASW Statistics 18. We will use the last observation carried forward to impute missing data and will report analyses with and without imputation. We will inform participants that they can leave the study at any time. We will report missing data, if applicable, by categorizing the participants as follows: mistakenly randomized, did not receive the intervention, withdrew consent, crossed over, dropped out, did not adhere, lost contact or other reasons not specified [33].

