### Study strengths and limitations

Currently — and despite the importance of maintaining the knowledge and skills of healthcare professionals — conventional approaches to continuing professional development (lectures, meetings) seem insufficient to translate learning to practice [35, 36]. We will experimentally test an innovative learning intervention based on a COP in the field of patient empowerment, for which the literature lacks experimental evaluations. This project, furthermore, proposes a COP in a virtual format, using technology to facilitate communication between COP members in different geographic locations and even different time zones, thereby increasing the diversity of the network [37].

A virtual COP offers theoretical and tangible benefits for improving professional knowledge and implementation in clinical practice [37], as follows:It is a unique, dynamic, semi-structured system set within an environment of continuous learning and offering immediate access to a broad range of knowledge.It offers access to repositories of current or historical discussions (archived knowledge) and enables access to peer or senior professionals regarding the application of appropriate knowledge in practice.It acts as a common platform for the discussion and exchange of ideas and resources (documents, data, audio files, videos, etc) aimed at ensuring optimal patient care.

Many training activities in the healthcare sector are currently designed for only one discipline or profession and so do not address the need for the perspective of inter-professional teams practising in these systems or settings [38–40]. In the experience of healthcare professionals, it appears that interacting with peers fosters learning and information sharing [16]. The e-MPODERA project will facilitate such inter-professional interactions.

We will run the clinical trial in three regions that are broadly representative of the Spanish national healthcare system, with publicly funded care models and different healthcare management models. Primary healthcare professionals across Spain — mainly GPs and nurses — have similar curricula (in terms of degrees and diplomas) and the GP specialization is based on similar training programmes. During the trial we will only allow the selected PCPs access to the COP, so as to limit the “viral” potential of the COP. Opening a second phase of open-access COP will control this limitation.

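### Allocation is balanced within three regions, but neither stated comparison of the primary outcome names region; adding it is a free improvement worth at most a few power points.

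*Protocol article*

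**What the plan says.** The Randomization section of the Protocol article restricts allocation by region: the 54 practices are assigned as "nine pairs for each of the three regions, each randomly assigned a code". The two arms have "27 PCPs per group) using Epidat 4.1 software (balanced group option". Nine pairs in each of three regions is 9 × 2 × 3 = 54 practices, so each region contributes nine practices to each arm.

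The Additional measures section lists the Spanish region of each professional as a baseline variable, separately from professional profile, which it defines as speciality, care setting and years of experience.

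The section on data collection, management and analyses gives two comparisons for PPOS. One is a Mann-Whitney U test, described without strata. The other is a multilevel model for the change in PPOS with the intervention indicator, a random effect and a propensity score. On covariates it says: "This model considers covariates such as age, sex and professional profile". The variables in the propensity score are not listed. The multilevel model is specified for PPOS only.

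**The concern.** Region is a factor on which the allocation is explicitly balanced, and it appears in neither comparison as described. Balancing within region removes regional variation from the true sampling variance of the treatment contrast. An analysis that ignores region still counts that variation as error. The effect estimate remains unbiased, but its standard error is too large, the confidence interval too wide and the test conservative.

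There is some reason to think that change could differ by region. The control arm follows the training plan of its own region (Control group section), and the limitations section notes "different healthcare management models" across the three regions. What is at stake is precision and power, not bias or an inflated type I error.

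**Working it through.** **The plan's own sample size.** Inputs from the Sample size section: "a post-intervention mean difference of 0.2 points and a common standard deviation of 0.5 points in the PPOS questionnaire"; "Each group will need 100 professionals, assuming alpha error of 0.05 and power of 80"%; "Considering an intraclass correlation coefficient of 0.03 and assuming an average size per cluster of five healthcare professionals".

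- Two-sided comparison of two means with difference 0.2 and SD 0.5: 99 per group (99.1 by the t-test formula), against 100 stated.
- Design effect: 1 + (5 − 1) × 0.03 = 1.12, as stated.
- 100 × 1.12 × 1.2 = 134.4, rounded up to 135 per group and 270 in total. This reproduces the stated figure. Nothing in it takes credit for balancing on region.

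**Cluster size at analysis.** 270 / 54 = 5 professionals per practice; after 20% loss, 5 × 0.8 = 4. The random effect is taken to be that of the practice.

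**Variance with and without region.** In units of the total variance (0.5² = 0.25), the variance of a practice mean is ICC + (1 − ICC)/m = 0.03 + 0.97/4 = 0.2725. If a share f of the between-practice variance lies between regions, adjustment leaves 0.03(1 − f) + 0.2425. The share f is an assumption.

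| f | Variance with region | Excess as share of reported variance | Reduction in SE |
|---|---|---|---|
| 0 | 0.2725 | 0% | 0% |
| 0.25 | 0.2650 | 0.0075/0.2725 = 2.8% | 1.4% |
| 0.50 | 0.2575 | 0.0150/0.2725 = 5.5% | 2.8% |
| 0.75 | 0.2500 | 0.0225/0.2725 = 8.3% | 4.2% |

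**Power.** SE = √(2 × 0.25 × variance / 27), which is 0.0710 without region and 0.0701, 0.0691 and 0.0680 with it.

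- Normal approximation, power = Φ(0.2/SE − 1.96): 80.4% from the unadjusted SE; 81.5%, 82.5% and 83.6% with region. The gains are about 1, 2 and 3 points.
- A stricter count lets the unadjusted test keep its wide SE while the estimate varies with the smaller true SE. Power without region is then Φ((0.2 − 1.96 × 0.0710)/SE), or 80.7%, 81.1% and 81.4%. The loss is about 0.7, 1.5 and 2.2 points.

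**Simulation check.** Practice means with 9 practices per region per arm, 4 professionals per practice, total SD 0.5, ICC 0.03 within region, and 20,000 runs per scenario. Region's share is expressed here as a share of total variance.

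| Region share of total variance | Power without region | Power with region | Type I error without region |
|---|---|---|---|
| 0% | 79.5% | 79.3% | 4.8% |
| 1% | 78.3% | 79.4% | 4.5% |
| 2% | 77.4% | 79.6% | 4.1% |
| 5% | 74.9% | 80.7% | 3.1% |
| 10% | 71.7% | 82.9% | 1.9% |

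The values f = 0.25 and 0.75 correspond to 0.03 × 0.25 = 0.75% and 0.03 × 0.75 = 2.25% of total variance. The 1% and 2% rows are therefore the comparable ones, with losses of 1.1 and 2.2 points. With region in the model, type I error was close to 5% in every scenario.

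**The case against.** The strongest objection is that the protocol never says region is left out. The covariates are given as examples, the propensity score has unlisted variables that could include region, and an article may leave the full list to the analysis plan. This stands. A reader might infer that the primary model omits region and throws away the precision of the design; the text supports only that region is not named. It remains reasonable to ask for the factor that structured the allocation to be fixed in advance rather than left to an open list.

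Second, the response is a change score, so stable regional differences in PPOS level cancel. Only differences in 12-month change matter, and the documents give no figure for them. The limitations section also describes curricula and GP training as similar across Spain, which points towards small differences. This stands too: the loss may be close to zero.

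Third, the larger losses in the simulation (about 6 points at a 5% share, 11 at 10%) require region alone to exceed the whole between-practice variance of 3% on which the plan is built. They should not be read as the expected size.

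A reader might also infer a much larger loss for PAM, on the ground that between-practice variance dominates there. The documents do not support this. They give no ICC for PAM and describe no multilevel model for it. With 1382 × 0.8 / 54 ≈ 20 patients per practice and the PPOS value of 0.03 borrowed as an assumption, between-practice variance is 0.03 / (0.03 + 0.97/20) = 38% of the variance of a practice mean, which is not dominant.

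**Conclusion.** The point holds as a free improvement. Allocation is balanced within three regions, and neither the PPOS model nor the Mann-Whitney comparison, as described, reflects those strata. If regions differ in PPOS change, an analysis without region is unbiased but conservative. With region explaining 25% to 75% of between-practice variance (assumed), ICC 0.03 and 4 completers per practice, the excess is roughly 3% to 8% of the reported variance, or about 1 to 3 power points. If they do not differ, there is no loss. No stated figure is wrong, and the sample size of 270 does not depend on this point.

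**What to change.** - Name region (3 levels) as a prespecified fixed effect in the PPOS mixed model.
- Stratify any rank-based comparison of the arms by region.
- Include region in whatever model is used for PAM.
- State whether the nine pairs per region were matched on practice characteristics or only served to balance numbers. If they were truly matched, reflect the pairing in the analysis as well.

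The region term costs two degrees of freedom among 54 practices and uses data already collected. If regions do not differ, the simulated price is negligible (79.3% power against 79.5%). Sample size and conduct are unaffected.
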